During development, drafts of the workbook were sent to an advisory panel of perinatal experts (psychologists, psychiatrists and midwives) for comments and feedback. A draft was also sent to a panel of service users who were part of an advisory group to a larger perinatal study. These women provided feedback on wording, relevance and use of examples and layout, and the workbook was modified accordingly. The workbook was piloted by one of the authors (JD) in routine IAPT care; ten women took part in the pilot to assess the feasibility of delivering the intervention during pregnancy, the acceptability of the content to pregnant women and preliminary outcomes. Based on women’s feedback, a number of amendments were made: the text was edited to reduce the number of words; the title was changed to ‘Wellbeing in Pregnancy’ (several women commented on the original title of the workbook, ‘Antenatal Depression’, which they felt was unhelpful due to possible stigma and their associations with more severe forms of perinatal disorders); specific references were made to how different sections were relevant to women who already have children; and the health chapter was adapted to be more focussed on overcoming barriers to good health behaviours (several women felt the chapter on health repeated messages they had from midwives and had less of a warm tone than other chapters). Women reported needing the sessions to motivate them and engage with the material; i.e. they indicated that they may not have completed the workbook on their own. The routinely collected scores on measures of anxiety (GAD-7) and depression (PHQ-9 and EPDS) reduced following the intervention.

Prior to delivering this Guided Self Help intervention within this pilot RCT, the two PWPs were trained in the modified intervention (and subsequently supervised on a weekly basis) by an experienced perinatal clinical psychologist. They were also trained in associated areas relevant to perinatal clinical work including safeguarding, violence and abuse, smoking cessation and the mother-child relationship [21]. The two PWPs will collect the same standardised measures as they would within an IAPT setting — Patient Health Questionnaire (PHQ-9), the Generalised Anxiety Disorder scale (GAD-7), the Work and Social Adjustment Scale and Phobia Scales — at every Guided Self Help session they have with trial participants.

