### Key secondary outcomes

#### At 14 weeks post-randomisation

At 14 weeks post-randomisation, the secondary outcomes are:Proportion of participants meeting PHQ-9 criteria for depression (i.e. score of ≥10)Proportion of participants meeting GAD-7 criteria for anxiety (i.e. score of ≥8).

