## Sample size

This is primarily a feasibility trial, but we also carried out a sample size calculation to allow us to calculate what preliminary evidence we could generate on efficacy. Assuming a correlation of 0.4 between baseline and outcome EPDS symptom score, a two-arm parallel-group design with 52 women in each arm, the Stata procedure *sampsi* gives 79 % power to detect a difference of 0.5 SD using ANCOVA and a two-tailed test using a 95 % significance level (based on an effect size of 0.31, as this was found in a systematic review of Guided Self Help in non-maternity settings [22]). We aim to recruit 110 women. The study would have 66 % power to detect a difference in the caseness rate of recovery of 35 % in controls versus 60 % in the Guided Self Help arm.

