An odds ratio and 95 % CI for recovery, defined within IAPT as a PHQ-9 score of ≥10 at 14 weeks post-randomisation, will be estimated. We will compare groups for continuous scores on the EPDS at 14 weeks post-randomisation and 3 months post-delivery. The variance estimates will assist in power calculations for a definitive trial. Supplementary analyses will estimate complier average causal effects for a binary measure of compliance to treatment using the instrumental variable method. Therapist effects will be evaluated. Infant growth will be explored using random effects growth curve models (*xtmixed* in Stata) to compare birth and growth velocities of the groups.

Qualitative data will be coded in NVivo8 [37] following the principles of framework analysis [38], which includes the identification of a thematic framework, the abstraction and synthesis of key themes and the mapping and interpretation of the dataset as a whole. Qualitative results will be discussed within the context of quantitative data interpretation.

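### The analysis section defines recovery as PHQ-9 ≥10, the cut-off the outcomes section uses for depression, so the planned odds ratio for recovery is inverted

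*Protocol article*

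**What the plan says.** Four places in the protocol article bear on this.

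- **Statistical analysis:** an odds ratio with a 95% confidence interval is planned for recovery, "defined within IAPT as a PHQ-9 score of ≥10 at 14 weeks post-randomisation".
- **Key secondary outcomes, at 14 weeks post-randomisation:** "Proportion of participants meeting PHQ-9 criteria for depression (i.e. score of ≥10").
- **Sample size:** the study is powered for "a difference in the caseness rate of recovery of 35 % in controls versus 60 % in the Guided Self Help arm". The section does not name the instrument behind these rates.
- **Modified Guided Self Help (with usual care) for antenatal depression**, on the workbook pilot: "The routinely collected scores on measures of anxiety (GAD-7) and depression (PHQ-9 and EPDS) reduced following the intervention". A fall in PHQ-9 is presented as improvement.

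Nothing elsewhere in the article reverses or explains the wording in the analysis section.

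**The concern.** The outcomes section and the analysis section agree on the scale, the threshold, the inequality sign and the visit, but attach opposite labels. A woman scoring 10 or more at 14 weeks would be both depressed and recovered. The sentence in the analysis section fixes the event for the odds ratio. If an analyst codes it literally, an effective intervention yields an odds ratio for recovery below 1, which a reader would take as harm.

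The Sample size section does not settle the matter cleanly, because its wording joins the two opposite terms: "power to detect a difference in the caseness rate of recovery". Read as recovery, 35% against 60% favours Guided Self Help. Read as caseness, the same figures would favour control.

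**Working it through.** **Inputs.** All are from the protocol article: recovery 35% in controls and 60% with Guided Self Help, stated power 66%, 52 women per arm, and a two-tailed test (all Sample size). Alpha is taken as 0.05, which is how I read the article's 95% significance level.

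**Step 1: reproduce the stated power.** I used the two-proportion test with pooled variance and the Fleiss continuity correction, with d = 0.60 − 0.35 = 0.25.

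- Effective n per arm: n₀ = (n·d − 1)² / (n·d²) = (13 − 1)² / (52 × 0.0625) = 144 / 3.25 = 44.3.
- Mean proportion: (0.35 + 0.60)/2 = 0.475.
- z = [0.25 × √44.31 − 1.96 × √(2 × 0.475 × 0.525)] / √(0.35 × 0.65 + 0.60 × 0.40) = (1.664 − 1.384) / 0.684 = 0.41.
- Power = Φ(0.41) = 65.9%, which matches the stated 66%.

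Without the correction, power at 52 per arm is 73.0%, so the corrected version is the one the article appears to use.

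**Step 2: reverse the event.** The complements are 65% in controls and 40% with Guided Self Help. The difference is again 0.25 in size. The mean proportion is 0.525, so the product 0.525 × 0.475 is the same, and so are the two binomial variances. Power is again 65.9%.

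**Step 3: odds ratio, Guided Self Help against control, 52 per arm.**

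| Event | Guided Self Help | Control | Odds ratio | Expected 95% CI |
|---|---|---|---|---|
| PHQ-9 <10 | 60% | 35% | (0.60/0.40)/(0.35/0.65) = 2.79 | 1.26 to 6.17 |
| PHQ-9 ≥10, as written | 40% | 65% | (0.40/0.60)/(0.65/0.35) = 0.36 | 0.16 to 0.80 |

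The standard error of the log odds ratio is √(1/31.2 + 1/20.8 + 1/18.2 + 1/33.8) = 0.406 in both rows. The estimates are exact reciprocals, and |log OR| / SE = 1.024 / 0.406 = 2.52 in both, so the p-value is the same.

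**Step 4: which passage is wrong.** The pilot text shows that lower PHQ-9 is better. The outcomes section is consistent with that, and so is the Sample size section when its rates are read as recovery. Only the analysis section runs the other way. No outside source for the IAPT definition is needed to reach this.

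**The case against.** The best defence is that this is a recognisable slip of the inequality sign. The outcomes section has the direction right, the sample size section treats recovery as the good result, and the outcome is secondary in a trial that describes itself as primarily a feasibility study. A careful analyst would probably notice. That limits the seriousness, but it does not make the sentence correct: it is the place where the event is defined for analysis, and no other passage overrides it.

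Three stronger readings are tempting, and the documents do not support them.

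- **That the power figure falls with the definition.** It does not. Step 2 shows that power is the same for either event. The Sample size section also does not say that its rates are based on PHQ-9, so applying them to this outcome is itself an inference.
- **That women already below 10 at entry dilute the effect and reduce power.** Entry is by SCID diagnosis with no minimum PHQ-9, so such women may exist. The article gives no baseline PHQ-9 distribution. Any size for the dilution would need an assumed share of such women, an assumed course for them in each arm, and a reading of 35% and 60% as rates among baseline cases only. The article states those rates for the arms without restriction; if they are whole-sample rates, no dilution follows.
- **That recovery must be restricted to women who were cases at baseline.** Comparing all randomised women at 14 weeks is a valid intention-to-treat comparison and fits the outcome as listed. Restricting the denominator changes the question and drops randomised women. It does not correct an error. The article gives nothing on the IAPT definition beyond the disputed sentence, so it cannot be used to require the restriction.

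**Conclusion.** The contradiction stands. The analysis section labels as recovery the score that the outcomes section labels as depression, and the analysis section is the one that is reversed. At the article's own planning rates the reported odds ratio would be 0.36 instead of 2.79, with the confidence interval inverted in the same way, so a benefit would read as lower odds of recovery. These sizes assume that the 35% and 60% rates apply to PHQ-9 recovery. The reversal itself does not depend on that assumption.

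The damage is confined to the direction and label of one secondary, exploratory estimate. The p-value, the 66% power and the primary EPDS regression are unaffected. It should still be corrected, because the sentence is wrong as written and would mislead if followed.

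**What to change.** In the Statistical analysis section, define recovery as PHQ-9 <10 at 14 weeks post-randomisation in all randomised women. Alternatively, keep ≥10 and name the outcome depression caseness. In either case:

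- state which event is modelled and which arm is in the numerator of the odds ratio;
- use the same direction in the key secondary outcomes, the sample size and the analysis sections;
- reword the sample size sentence so that it refers to recovery or to caseness, not both.

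The cost is a sentence or two. Sample size, data collection and the primary analysis stay as they are. If the team wants to know how women with baseline PHQ-9 ≥10 fared, that can be added as an optional sensitivity analysis with its smaller denominator stated; it is not needed for this correction.

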## Economic evaluation

The economic evaluation will take the NHS and personal social services perspective preferred by NICE [39]. Resource use data from the AD-SUS (see Additional file 4: Table S2 for full details of the AD-SUS measure) will be combined with unit costs to calculate total costs of the Guided Self Help and usual care groups. The cost of Guided Self Help will be calculated using a micro-costing approach based on the PWPs’ salary, including relevant on-costs and overheads. Unit costs of other services will be taken from national published sources.

Exploratory economic analyses, on an intention-to-treat basis, will include tests for differences in cost using standard parametric *t* tests with the validity of results confirmed using bias-corrected, nonparametric bootstrapping (repeat re-sampling) [40]. Cost-effectiveness will be assessed through the calculation of incremental cost-effectiveness ratios [41] and will be explored in terms of quality-adjusted life years using the SF-6D (derived from the 36 item Short Form Health Survey (SF-36)). A sensitivity analysis will be performed using the EuroQoL five dimensions questionnaire (EQ-5D), and a formal assessment of the validity and responsiveness of both the SF-6D and EQ-5D will be undertaken following standard methods [42, 43]. All regressions to calculate mean differences in costs will be repeated with the further inclusion of covariates for baseline clinical measures. Uncertainty around the cost and effectiveness estimates will be represented by cost-effectiveness acceptability curves [44]. Should the results of the trial support the use of Guided Self Help as an effective and cost-effective treatment option for mild and moderate antenatal depression, data from the trial will be used to re-run the economic decision model from a related study (WENDY- http://www.kcl.ac.uk/ioppn/depts/hspr/research/CEPH/wmh/projects/A-Z/WENDY-well-being-in-pregnancy-in-an-inner-city-maternity-service.aspx) in order to explore the relative cost-effectiveness of the alternative screening approaches when Guided Self Help is incorporated into the treatment pathway for this group of women.

## Discussion

The DAWN trial is the first exploratory trial to our knowledge to investigate the efficacy of antenatal Guided Self Help for pregnant women diagnosed with mild to moderate depression. As part of a larger National Institute for Health Research (NIHR)-funded programme of research (see http://www.kcl.ac.uk/ioppn/depts/hspr/research/CEPH/wmh/projects/A-Z/esmi.aspx), independent oversight is provided by a Programme Steering Committee, Programme Data Monitoring and Ethics Committee (DMEC) and Trial Steering Committee (TSC). The UKCRC registered King’s College London (KCL) Clinical Trials Unit provides web-based data entry systems using the InferMed MACRO data entry system which is compliant with Good Clinical Practice (GCP) and Food and Drug Administration (FDA) 21 Code of Federal Regulations (CFR) Part 11. No interim analyses are planned. Only the trial investigators and the TSC and DMEC, if any adverse or other unintended effects are identified, will have access to participants’ personal data. We will collect, assess, report and manage any adverse events that may occur. Any adverse events or other unintended effects of the trial intervention or conduct will be recorded and reported to the DMEC (DMEC charter available from author).

## Ethical issues

A number of practical measures have been taken to minimise distress and risk to participants. These include the following:When taking consent, researchers will explain to participants that they can take time in answering questions and do not have to answer questions that they do not want to.At the baseline interview, researchers will ask participants if they would like to nominate a contact for support, should they become distressed.During the interview, researchers will closely monitor participants for signs of distress and, if observed, will take appropriate action, including asking the participant if she would like to take a short break, skipping questions that cause particular distress, or offering to complete the interview at another time.

Safety protocols have been developed to ensure that participants, their families and the researcher remain safe when making contact, conducting research and afterwards. On initial contact, researchers will establish an appropriate contact number and time for future contact between themselves and participants; if participants would like to keep their participation in the research confidential from other people, researchers will establish how to manage the situation if conversations are overheard (e.g. they can start discussing safety of electrical appliances in the home). This is done because there is a risk that telephone conversations may still be overheard. At all points of contact, researchers will confirm that they are speaking with the participant and will not leave information with any other household member, unless the participant has specified that this is okay. The identity of the researchers will not be given to any caller until the identity of the caller has been established. Researchers will ensure that the location(s) where an interview takes place is private and secure and cannot be overheard. Interviews will be conducted either in a secure room at the NHS Trust or, if deemed safe, at the participant’s home. If interviews are to take place at a participant’s home, the researcher will first discuss any immediate or peripheral safety issues with support providers or relevant professionals and clarify if it is safe for them to conduct interviews in the home. Researchers will have access to a mobile phone and screech alarm at all times during interviews and will give details of interview locations, start times and approximate end times to colleagues at their research department. After the interviews, researchers will ask the participants how they feel and if they would like to discuss anything further with their responsible clinician.

### Confidentiality

All participants will be interviewed in private by trained researchers. The information provided by participants will be confidential and anonymised. In some situations, however, it may be necessary to disclose personal information without a patient’s consent if it is in the public interest (i.e. where a failure to do so may expose the patient or others to risk of death or serious harm). The limits of confidentiality are explained on the participant information sheet and will be discussed with all participants as part of the informed consent process. The General Medical Council guidance on confidentiality will be followed [45]; disclosure of personal information without consent may be justified in the public interest where failure to do so may expose the patient or others to risk of death or serious harm. In cases where the patient or others are exposed to a risk so serious that it outweighs the patient’s privacy interest, consent to disclose will be sought. If it is not practicable to obtain consent, the information will be disclosed to an appropriate person or authority. The researchers will contact one of the clinical applicants on the grant to discuss any situations when confidentiality may need to be broken. Detailed guidance on safeguarding maternal and child welfare is outlined in the Programme-wide Standard Operating Procedures.

### Trial status

The trial is currently recruiting.

## Appendix

### Psychological Wellbeing Practitioner perinatal competencies for the DAWN trial

A pre-requisite for working on the trial was that the Psychological Wellbeing Practitioners (PWPs) had completed PWP (IAPT) low intensity training and had acquired a Postgraduate Certificate in Low Intensity Cognitive Behavioural Interventions according to the National Curriculum for the Education of Psychological Wellbeing Practitioners (now the 3^rd^ edition, 2015). On appointment to the trial, the PWPs received training to cover competencies relevant to working with women during the perinatal period, as specified below.

### Knowledge of pregnancy, childbirth and the postnatal period

This competency includes knowledge of:

- Physical and emotional changes during the perinatal period
- Common complications of pregnancy, childbirth and the postnatal period
- Routine maternity and obstetric care

### Knowledge of mental health during the perinatal period

This competency includes knowledge of:

- Prevalence of mental health problems; risk of relapse; the impact of mental health problems on the infant
- Understanding of the importance of prevention and early intervention and the role of specialist perinatal mental health services
- Knowledge of depression and anxiety disorders and how they may present in the perinatal period as well as how their course can fluctuate in response to events in the perinatal period
- Knowledge of serious mental health problems and how they may present in the perinatal period including bipolar disorder and post-partum psychosis.

### Understanding of the parent-infant relationship

This competency involves awareness of issues relating to infant mental health, attachment and parenting (including the ways in which experiences of being parented are relevant when becoming a parent).

### Therapeutic competencies relating to the perinatal period

These competencies include:

- The ability to support women using Guided Self Help materials with adaptations for the perinatal period
- Knowledge of behavioural activation that is appropriate for the woman’s goals, her stage of pregnancy or for the postnatal period allowing for taking care of the baby
- Knowledge of relaxation techniques
- Knowledge of Guided Self Help interventions to increase the availability of interpersonal support
- The ability to work with cognitions and beliefs about the baby/about self as a parent
- Knowledge of Guided Self Help interventions relating to health and lifestyle.

### Metacompetencies

Metacompetencies include planning and delivering treatment in a flexible manner, including adjusting to unanticipated events during pregnancy or postnatally.

### Professional, ethical and legal issues

This competency includes:

- Knowledge of IAPT including criteria for stepping up and down relevant to the perinatal period
- Knowledge of local specialist perinatal services, referral routes and care pathways
- Awareness of national and local organisations relevant to the perinatal period
- Ability to liaise with other agencies such as maternity services, health visitors and social care
- Knowledge of safeguarding, including assessing and managing risks to the unborn infant and making referrals to Social Care
- Ability to administer, score and interpret routine outcome measures
- Awareness of issues relating to consent and confidentiality
- Awareness of equality and diversity, including cultural differences in parenting, same sex couples and single parents.

### DAWN trial induction and specialist training

This training includes:

- Overview of perinatal mental health
- Adaptations of CBT and common themes in the perinatal period
- Use of the workbook
- Supporting Infant Mental Health
- Safeguarding Children Level 3
- Domestic Abuse Awareness
- Smoking Cessation
- Smoking Cessation in Pregnancy and the Postpartum Period
- Observing a booking appointment
- Visit to the antenatal and postnatal wards.

## Abbreviations

CBT: Cognitive behavioural therapy
DMEC: Data Monitoring and Ethics Committee
EPDS: Edinburgh Postnatal Depression Scale
GAD-7: Generalised Anxiety Disorder scale
IAPT: Improving Access to Psychological Therapies
NICE: National Institute for Health and Care Excellence
PHQ-9: Patient Health Questionnaire
PWP: Psychological Wellbeing Practitioner
REC: Research Ethics Committee
SCID: Structured Clinical Interview DSM-IV
